### Determining drivers of SAIA-TB intervention implementation heterogeneity

We will apply four implementation science theories, models, and frameworks to examine the implementation process, focusing on clinics as the organizational level.

#### Organizational Readiness for Implementing Change

Organizational Readiness for Implementing Change (ORIC) assesses the extent to which organizational members are psychologically and behaviorally prepared to implement organizational change, affecting decisions to adopt implementation strategies such as SAIA-TB [61, 62]. Readiness includes (1) change commitment, a shared resolve to implement a change, and (2) change efficacy, a shared belief in the collective capability to implement a change. Therefore, to understand readiness for adopting SAIA-TB, we will apply the ORIC assessment scale to at least 6 health workers per study facility (*n* = 48) and district and provincial management (*n* = 12). Analysis will test whether sufficient inter-rater reliability and inter-rater agreement exist to aggregate individual responses to the facility level; if tests do not justify aggregation, we will use a measure of intra-facility variability in readiness rather than a facility-level mean in analysis. This will provide readiness profiles for each facility as they initiate implementation, complementing adoption, implementation, and effectiveness data in understanding the broad impact of SAIA-TB. The ORIC assessments have been used in many SAIA settings as well as in other contexts by the study team and in South Africa [63–65].

#### Facility-level structural readiness assessments

Standardized readiness assessments, adapted and abbreviated from the service availability and readiness assessment (SARA) tool, will be carried out immediately prior to each phase (baseline, intervention, maintenance) in all 16 study facilities to assess structural readiness to deliver TB services (staffing levels, attributes and training, availability of essential commodities, equipment, supplies, and clinic infrastructure) [66]. This adapted tool has been piloted in a neighboring Eastern Cape district for TB services by the study team. These facility-level assessments will help inform what drove implementation success or failure and to examine if structural changes took place during the study period beyond TB services.

#### Consolidated Framework for Implementation Research

We will use the Consolidated Framework for Implementation Research (CFIR) to guide an in-depth examination of the implementation process, define SAIA-TB core components, and describe determinants of implementation success and failure across implementing local municipalities and facilities [67]. The study team has experience in using CFIR for TB in the South African context, and in prior SAIA trials, and discussion guides will be developed using available CFIR tools to gather data about constructs from the five CFIR domains plus an added systems domain used in low-resource settings [44, 68, 69]. After the completion of the intervention phase, and receiving written consent from participants, we will conduct focus group discussions (FGDs) in each intervention facility with 6–8 clinic staff (sufficient to generate conversation without being too large to become intimidating) (*n* = 96–128) participating in SAIA-TB [70]. Facilities will be classified as either high or low performing (identified by facilities’ fidelity to the SAIA-TB intervention, defined as the number and frequency of SAIA-TB cycles conducted, and the consistent use of quantitative CQI data to inform progress). Focus group discussions will be purposively held by individual facilities in order to classify them as high and low implementation fidelity and to uncover salient features of successful implementation. In-depth interviews (IDIs) will also be conducted with facility (*n* = 16) and district and provincial (*n* = 12) managers participating in SAIA-TB. These IDIs will allow for the collection of potentially sensitive information from leadership that might otherwise might not be shared in a larger group, and to give lower-ranking team members more freedom to speak freely in the FGDs, regarding leadership engagement or organizational culture or hierarchy. The IDIs allow for the capture of individual experience with disseminating and implementing SAIA-TB and capture intervention adaptations over time, such as staff attitudes or identification with the organization. Participants will be purposively selected for a balance of individuals across service locations and roles within the facilities (i.e., nursing, pharmacy, reception, social work, community health workers). We will repeat an equal number of FGDs and IDIs at the end of the maintenance phase to explore the implementation process and adaption that occurred during that period. The same sampling scheme will be used.

Interviews (FGDs and IDIs) will be conducted in English (the working language across South Africa) by an experienced facilitator, audio-recorded, and transcribed verbatim. Focus groups will also have a note taker present. Two coders in a stepwise, iterative process will code transcripts and conduct content analysis within a deductive framework to identify key implementation themes using selected CFIR constructs, yet allowing flexibility for additional themes to emerge. Coding will be compared across pairs and differences discussed prior to final coding. Case memos will be documented and three analysts will assign ratings for each construct. Ratings will reflect the positive or negative influence (valence) and strength of each construct, as previous applications of CFIR have shown [43, 71]. Finally, constructs will be coded as missing too much data (M), not (0), weakly (+ 1/ − 1), or strongly (+ 2/ − 2) distinguishing low/high performance. These qualitative findings will be used to develop recommendations for SAIA-TB implementation, specific to its core components, intervention adaptions, and lessons learned.

#### Implementation fidelity

We will prospectively document fidelity to the protocol and track implementation using surveys filled out by study nurses and study data clerks. We will capture the following: number of planning sessions each facility conducted, number of participants in sessions, number of workflow modifications tested, and the content and results of modifications.

#### Maintenance

We will measure the extent to which SAIA-TB is maintained over time at the organizational (i.e., facility) level. This will be measured as the proportion of facilities continuing to implement the intervention as designed. We will describe the proportion of local municipalities (clusters) and facilities continuing to implement SAIA-TB at 6 and 12 months post-intervention (target: > 90% at 6 months, > 75% at 12 months). Continued maintenance is defined as holding monthly SAIA-TB meetings. We will also evaluate maintenance through in-depth interviews and focus group discussions with district and facility staff on perspectives of determinants of sustained implementation or barriers to maintenance at the end of the maintenance phase as described above.

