### SAIA-TB trial design

This study is a 5-year, four-wave stepped wedge cluster randomized trial design to assess the effectiveness of the SAIA-TB strategy (Fig. 1; Consort Checklist, Additional file 1). Each wave includes four local municipalities within a district, with four health facilities per local municipality purposively selected to receive SAIA for a total of 16 facilities. Each local municipality represents a cluster and will be randomized for intervention wave. Each facility will have at least 12 months of baseline data collection followed by 18 months of intervention and 12 months of a measured maintenance phase (Fig. 3).

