#### Maintenance phase

During the final 12-month period, SAIA-TB will have a *maintenance phase*, whereby monthly visits will continue by district authorities without study personnel to evaluate SAIA-TB’s sustainability with moderate resource investment.

It is expected that SAIA cycles will continue to occur monthly, with an average of 12 SAIA cycles per year per facility. A SAIA core component that will be maintained in SAIA-TB is provision of a flexible clinic support fund to address equipment needs for TB management (scales, some transportation costs for patients, etc.) as well as to support smaller workflow modifications, which will continue throughout both the intervention and maintenance periods. During monthly visits, facility staff participating in the intervention will complete questionnaires measuring drivers of SAIA-TB and participate in facilitation of process mapping, supportive clinical consultations, and systems engineering discussions.

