#### Eligibility criteria

This study will take place in four local municipalities within the Sarah Baartman district, Eastern Cape, South Africa (Fig. 5). Services for TB across South Africa are primarily provided through the public sector, and all proposed study clinics are public. Study clinics are evenly split across four local municipalities in Sarah Baartman district—Ndlambe, Sundays River Valley, Kou-Kamma, and Kouga (Table 1). These local municipalities were chosen in partnership with district of health officials for their heterogeneity in populations, proximity to Gqeberha (within 2 h’ drive to where the study office is located), patient volume (at least 4500 outpatient visits in 2022), rurality (mix of rural, semi-rural, semi-urban), and staffing mixture. Each clinic has at least two professional nurses, one or two pharmacy technicians, a data clerk, and a social worker, as well as multiple community health workers who are clinic-based or part of ward-based outreach teams.

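### Maintenance is described as continuing SAIA-TB as designed but scored only by monthly meetings held, and its paired targets do not work for four municipalities

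*Protocol article*

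**What the plan says.** The Maintenance section introduces the outcome with "This will be measured as the proportion of facilities continuing to implement the intervention as designed". It then says "We will describe the proportion of local municipalities (clusters) and facilities continuing to implement SAIA-TB at 6 and 12 months post-intervention", with the parenthesis "target: > 90% at 6 months, > 75% at 12 months", and gives the counting rule: "Continued maintenance is defined as holding monthly SAIA-TB meetings".

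Four other places bear on this:

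- **Components of SAIA-TB.** The last paragraph of the Background names the cascade analysis tool (TCAT), monthly process mapping and quality improvement cycles with clinic-chosen changes as core. Steps 1 to 5 of the strategy description set out the same elements.
- **Fidelity.** The Consolidated Framework for Implementation Research section defines fidelity by how many cycles are done and how often, and by whether quantitative improvement data are used consistently. The Implementation fidelity section plans to record "number of planning sessions each facility conducted, number of participants in sessions, number of workflow modifications tested", together with what the modifications were and what they achieved. Study nurses and study data clerks complete these surveys.
- **Conditions during maintenance.** The Maintenance phase section says "monthly visits will continue by district authorities without study personnel". The clinic support fund also continues.
- **Units.** The SAIA-TB trial design section gives "four health facilities per local municipality purposively selected to receive SAIA for a total of 16 facilities", and the Eligibility criteria section says "Study clinics are evenly split across four local municipalities in Sarah Baartman district".

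**The concern.** The sentence that names the outcome and the sentence that scores it ask for different things. The first asks whether the intervention is still delivered in its designed form. The second asks whether a monthly meeting took place. As written, the rule does not ask for a cascade review, a process map, a workflow change or any look at its result. A facility could be counted as continuing when some or all of these have lapsed.

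The maintenance phase is where the protocol sets out to evaluate sustainability. A proportion reported as implementation as designed will be read as evidence that the whole strategy lasted, when it shows only that meetings went on.

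The targets raise a smaller, separate problem. The 12-month target is lower than the 6-month one. With only four municipalities that difference may vanish, so the municipality result could be reported as a missed target for reasons of counting alone.

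**Working it through.** **1. The two definitions side by side**

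| Place in the protocol article | What a continuing or faithful facility must show |
|---|---|
| Maintenance, description of the outcome | Intervention implemented as designed |
| Background and Steps 1 to 5 | TCAT review, process mapping, a workflow change, monitoring of its result, repetition |
| Consolidated Framework for Implementation Research | Number and frequency of cycles, plus consistent use of improvement data |
| Implementation fidelity | Planning sessions, participants, modifications tested, their content and results |
| Maintenance, scoring rule | Monthly SAIA-TB meetings held |

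The last row is the operative rule. It matches at most one element of the rows above, the holding of sessions. The end-of-phase interviews and focus groups explore why maintenance succeeded or failed, but they do not change which facilities are counted.

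**2. When the readings are taken**

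The trial design section gives 12 months of maintenance after the intervention phase. The 6- and 12-month readings therefore both fall within the period of monthly district visits and the continuing fund. The visits have the same frequency as the scored meetings. That they help to bring the meetings about is a reasonable inference, not something the document states.

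**3. What the targets require**

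The targets are set values, so there is no calculation in the plan to reproduce. The unit count agrees: 4 × 4 = 16 facilities.

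The required count is the smallest whole number k with k/n strictly above the target.

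| Units | Target | n × target | Needed with > | Needed if ≥ were meant |
|---|---|---|---|---|
| 16 facilities | 90% at 6 months | 14.4 | 15 (93.75%) | 15 |
| 16 facilities | 75% at 12 months | 12 | 13 (81.25%) | 12 |
| 4 municipalities | 90% at 6 months | 3.6 | 4 (100%) | 4 |
| 4 municipalities | 75% at 12 months | 3 | 4 (100%) | 3 |

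With the printed sign, the facility targets stay distinct (15, then 13) and the municipality targets are identical (4, then 4).

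**4. When a municipality counts as continuing**

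The Maintenance section does not say, so the following rests on assumed rules.

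- **All four clinics must continue (assumed).** With 15 of 16 facilities at 6 months, the one lapsed clinic leaves 3/4 = 75% of municipalities: facility target met, municipality target missed. With 13 of 16 at 12 months, the three lapsed clinics leave 3/4 if they share a municipality and 1/4 if they lie in three different ones.
- **Any one clinic suffices (assumed).** Three lapsed clinics cannot empty a municipality of four, so 13 of 16 always gives 4/4.

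The same facility result can thus give anything from 1/4 to 4/4 municipalities, depending on a rule the section leaves open.

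**The case against.** The strongest reply is that the scoring sentence operationalises the first sentence and does not contradict it. What is counted is a SAIA-TB meeting, not any staff gathering. The Intervention phase section describes the first improvement meeting as one where a change is chosen and defined. The Maintenance phase section expects monthly cycles to go on and places process mapping and systems discussions within the monthly visits. Operating procedures not shown here may set the content of a meeting.

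Much of this stands. The rule is best called a coarse proxy. A reader might infer that all 16 clinics could score as maintained with no workflow modification ever tested. That assumes a SAIA-TB meeting has no required content, which the document does not say. What remains is that the article fixes a rule naming meetings alone, although it has a fuller fidelity definition available.

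A reader might also infer that the trial will declare SAIA-TB sustainable on this measure alone. The document does not support that. The proportion is to be described, with no test or decision tied to it. The maintenance phase is also covered by monthly cascade indicators, a separate segment of the time-series analysis, readiness assessments before the phase, and repeat interviews and focus groups at its end. Meetings with little content could show up there.

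Continuing district support is not a fault either. The Maintenance phase section says openly that sustainability is evaluated with a moderate level of resources. This affects how the result should be labelled, not whether the design is sound.

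On the targets, the section places maintenance at facility level, and the municipality clash depends on > as printed. Both points are fair. Even so, the sentence carrying the targets names municipalities first, and the printed sign is what a reader will apply.

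**Conclusion.** The concern holds in a limited form. Maintenance is presented as implementation as designed and scored as monthly meetings held, a standard below the protocol's own core components and fidelity definition. The reported proportion can only equal or exceed one that also required those elements. The size of any excess cannot be estimated from the document.

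The single pair of targets works for the 16 facilities (15 and 13) but not for the 4 municipalities, where both readings require 4 of 4. This rests on the strict sign; with ≥ the 12-month requirement would be 3 of 4. The conflict between facility and municipality results shown above also needs an assumed rule for when a municipality counts.

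This is a descriptive implementation outcome. Randomisation, the primary outcomes, power and the effectiveness analysis are untouched. The change is worth making before the maintenance phase begins.

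**What to change.** 1. **Scoring.** Count a facility as maintained from elements the protocol already has: monthly cycle conducted, cascade or improvement data used, workflow modifications recorded. Define a cycle by reference to Steps 1 to 5, so that process mapping is covered. Report monthly meetings held as a separate figure.
2. **Recording.** State who records these items during maintenance. The fidelity surveys are completed by study staff, the maintenance visits take place without study personnel, and the article does not say how the surveys continue.
3. **Minimum alternative.** If the scoring stays as it is, label the figure as monthly meetings held under continued district support, and drop the description of it as implementation as designed.
4. **Targets.** Apply the > 90% and > 75% targets to the 16 facilities only, written as 15/16 and 13/16. Report municipalities as counts out of 4 without a target, and state when a municipality counts as continuing.

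The cost is some rewording, a small addition to the fidelity form (the listed items do not include data use) and an agreed recorder for the maintenance phase. The maintenance figure will probably be less favourable.

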### Ethics

Approval by the institutional review board at Boston College was obtained (23.139.01). Additionally, approval was provided by the South African Medical Research Council (EC012-5/2023). The study was registered with the Eastern Cape Department of Health National Health Research Database (September 2023). This study was also registered with ClinicaTrials.gov, registration number NCT06314386.

### Study status

Implementation of the SAIA-TB intervention began in October 2023 with baseline facility assessments. At the time of submission, baseline data collection is occurring in all 16 clinics and the intense intervention phase is planned to start in January 2025.

## Discussion

At the completion of this pragmatic stepped wedge cluster randomized trial, important knowledge regarding the effectiveness of SAIA-TB on TB cascade optimization for patients with TB and high-risk contacts, specifically PLH in a high burden TB/HIV context will be gained. Drivers of SAIA-TB implementation variability across clinics and fidelity to the intervention will be better understood, providing robust evidence for translation, scale-up, and dissemination. Given the rapidly evolving landscape of TB guideline development on the global and national level, this intervention provides opportunity to be at the forefront of implementing newly released TPT regimens as they become available within the public sector. Our agility within the SAIA strategy provides clinics opportunity for knowledge sharing and innovation as we take lessons learned from the pandemic and translate and harness them for TB and HIV services [72, 73]. Finally, adaptations from previous SAIA iterations will be documented to aid in future SAIA implementation in additional health conditions and across geographically diverse settings.

## Data Availability

Not applicable.

## Abbreviations

CFIR: Consolidated Framework for Implementation Research
CQI: Continuous quality improvement
HIV: Human immunodeficiency virus
ORIC: Organizational Readiness for Implementing Change
SAIA: Systems analysis and improvement approach
TB: Tuberculosis
TCAT: Tuberculosis cascade analysis tool
WHO: World Health Organization
